### Study procedures and outcomes: duration of the treatment and follow up

2.2

In order to compare the proportions of solifenacin and mirabegron groups, the estimated sample size for each group has been calculated as 156 participants considering a normal distribution, an *α* error of 0.05 and a power of 80 percent. To evaluate mirabegron safety, cardiac and respiratory parameters (heart rate, blood pressure, oxygen saturation, respiratory support) will be monitored during every study visit. After obtaining informed consent and after the screening visit, at Baseline (T0) all patients will be evaluated with a complete ophthalmic examination. BCVA will be assessed based on the refractive values obtained using an autorefractometer (Huvitz autoref/keratometer HRK-1 Huvitz Co. Ltd., Republic of Korea), in agreement with Early Treatment Diabetic Retinopathy Study (ETDRS) charts. Intraocular pressure measurements will be acquired using the same device. Additionally, slit lamp examination and fundus examination by indirect ophthalmoscopy will be performed in all patients. As part of the imaging protocol, all patients will be evaluated using spectral domain optical coherence tomography (SD-OCT) and fundus autofluorescence (FAF) (SD-OCT Spectralis, Heidelberg Engineering, Heidelberg, Germany). Microperimetry will be performed using MP-1 microperimetry (Nidek Instruments Inc., Padova, Italy). All patients will be evaluated at T0, 6- and 12-months follow-up, with a complete ophthalmic examination, including SD-OCT, FAF, and microperimetry, and monitoring for any signs of ocular inflammation and/or any adverse events.

#### Primary outcomes

2.2.1

Primary outcomes include conversion to wet AMD at 12 months (assessed by the presence of intraretinal fluid, subretinal fluid, pigment epithelial detachment, subretinal hyperreflactiva material) and outer retinal morphology using SD-OCT and FAF, including reticular pseudodrusen (RPD) type, outer nuclear layer (ONL) thickness, choroidal thickness (ChT), central macular thickness (CMT) and FAF changes.

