## Introduction

1

Sensory impairments, including vision loss, are a part of normal aging that is associated with additional aging-related diseases including those characterized by reduced contractile activity, as in overactive bladder (OAB) wherein urgency and frequent micturition are driven by a multitude of anatomical, metabolic and psychological causes. Among vision impairments proliferative retinopathies including neovascular age-related macular degeneration (wet AMD) pose a significant global burden on individuals, families, and healthcare systems (1). Wet AMD is a major cause of vision loss in elderly people, with an increase in its prevalence in the population over 75 years old. Its estimated increase of about 47% from 2020 to 2040 (2) represents a significant burden to healthcare systems, both in terms of medical treatment and non-medical related costs, such as social services (3). Intravitreal injection of anti-vascular endothelial growth factor (anti-VEGF) is approved for wet AMD. Anti-VEGFs are effective in reducing exudation, but they require frequent injections that, on the other hand, might not be decisive in providing a solution.

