### Study design and participants: inclusion, exclusion and drop out criteria

2.1

We planned an observational double arm non-randomized study in two centers to compare the safety and efficacy of either mirabegron (50 mg/day) or solifenacin (5 mg/day) in OAB patients. The protocol provides that ophthalmologists will be blinded regarding which patients have been treated with both drugs. We planned to enroll 312 subjects aged between 50 and 80 years with a diagnosis of early or moderate dry AMD, according to ARDS classification, and OAB. The patients will be enrolled at the Department of Ophthalmology of the University of Lublin, Poland and the University of Naples Federico II, Italy from December 2025 to October 2026. All patients will be followed for a 12-month period. The study will be conducted in compliance with the tenets of the Declaration of Helsinki, accepted by the local Ethics Committee, protocol numbers 2025a45673 at the University of Naples Federico II, Italy and KE-0379/97/2025 at the University of Lublin, Poland.

All study participants will provide written informed consent prior to enrollment and for the use of their clinical data for scientific research in an anonymized manner. Inclusion and exclusion criteria are summarized in Table 1.

**Table 1 tab1:** Inclusion and exclusion criteria.

Inclusion criteria
Age 50–80-year-old
Patients with early or moderate dry AMD in one or both eyes
Patients with wet AMD in the other eye
OAB treated for at least 6 months with either mirabegron or solifenacin
BCVA > 65 EDTRS letters
Exclusion criteria
Any contraindication to β-agonists or anticholinergics
Allergy to β-agonists or anticholinergics
Uncontrolled hypertension; tachycardia; atrial fibrillation; long QT or concomitant treatment with drugs that cause lengthening of the QT interval
Patients exposed to experimental drugs other than mirabegron or solifenacin, complement factor inhibitors, photobiomodulation therapy, transscleral lutein iontophoresis therapy or recent surgery (e.g., 3 months)
Recurrent urinary infections
Renal or hepatic failure
Signs of ocular inflammation
Any other ophthalmic diseases such as dry eye, glaucoma, acute or chronic uveitis, advanced cataract
Pregnancy

AMD, age-related macular degeneration; OAB, overactive bladder; BCVA, best corrected visual acuity; EDTRS, early treatment diabetic retinopathy study; QT interval, the time from the start of the Q wave to the end of the T wave in an electrocardiogram.

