### Data analysis plan and statistical analysis

2.3

The sample size was estimated based on epidemiological data and previous literature on AMD progression using planning assumptions for 12 months conversion to wet AMD. Eligibility criteria are reported in Table 1; in brief, contralateral wet AMD status (yes/no) will be recorded at baseline given its strong influence on conversion risk. Published evidence indicates that conversion risk depends substantially on fellow-eye status. In high-risk fellow eyes of patients with unilateral wet AMD, Barbazetto et al. (20) reported a 12-month conversion rate of 20.3% in MARINA and 15.9% in ANCHOR studies. In large trial populations with wet AMD in the contralateral eye, fellow-eye analyses reported cumulative incidences of approximately 26.2–32.2% over 96 weeks (21–23). In contrast, in cohorts without wet AMD in the contralateral eye, annual conversion rates are lower; for example, Chakravarthy et al. (24) reported progression to choroidal neovascularization (CNV) of approximately 3.2 per 100 person-years in bilateral early/intermediate AMD, compared with 15.2 per 100 person-years when CNV was present in the fellow eye (25). Therefore, the expected 12-month conversion rate of 12% has been used as a planning value reflecting the anticipated mix of baseline risk strata in our eye-level cohort, rather than a single incidence applicable to all included eyes. Observed conversion will be reported as stratified by the contralateral wet AMD status (yes/no), and the contralateral status will be included as a key prognostic factor in adjusted analyses.

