Assuming a 12% progression rate in the solifenacin group and a 3% progression rate in the mirabegron group at 12 months (absolute difference 9%), with *α* = 0.05 (two-sided) and power = 80%, the required sample size is n ≈ 134 participants per group (net, without accounting for dropouts), computed using the standard formula for comparison of two proportions. The choice of the absolute difference of 9% is not based on clinical data as no clinical trials using either solifenacin or mirabegron to verify the rate of dry AMD progression to the wet form have been performed. This absolute difference was selected as a clinically meaningful planning effect size (Number Needed to Treat ≈ 11 over 12 months). Because eligibility and outcomes are defined at the eye level and participants may contribute with one or two eligible eyes, this calculation should be considered a planning approximation; all inferential analyses will account for within-participant correlation using robust standard errors clustered by participants.

To allow for an expected 15% dropout/non-compliance rate, the enrollment target was increased accordingly, yielding n ≈ 157 participants per group (314 total). For reporting and logistical reasons this has been pragmatically rounded to 156 participants per group (312 total); the protocol will state that this figure includes an allowance for approximately 15% attrition.

The sample size was computed according to the classical formula for two independent proportions:

$$n=\frac{\left(Z_{1-\frac{\alpha }{2}}\sqrt{2p(1-p)}+Z_{1-\beta }\sqrt{p_{1}(1-p_{1})+p_{2}{\left(1-p_{2}\right)}^{2}}\right)}{{\left(p_{1}-p_{2}\right)}^{2}}$$

Where *p*_1_ = 0.12, *p*_2_ = 0.03, *p* = (*p*_1_ + *p*_2_)/2, *α* = 0.05, and 1-*β* = 0.80. The resulting net sample size is approximately n ≈ 134 per group; after adjusting for ~15% attrition the enrollment target is *n* ≈ 157per group (rounded for the protocol to 156 per group).

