All statistical analyses will be done using Python in the Google Colab cloud computing environment and/or SPSS (version 31). The primary confirmatory timepoint will be 12 months. To control type 1 error across the pre-specified primary endpoints, *p*-values will be adjusted using the Holm procedure (two-sided). Statistical significance will be set at a two-sided α = 0.05. Analyses will be conducted using exposure-defined (as-treated) and protocol-adherent approaches, rather than randomized intention-to-treat terminology. Continuous variables will be summarized as mean ± standard deviation or median with interquartile range, depending on the data distribution assessed by the Shapiro–Wilk test. Categorical variables will be presented as frequencies and percentages. Baseline characteristics will be described and group balance will be assessed using standardized differences, rather than relying on significance testing of baseline differences.

The primary outcome measures include conversion to wet AMD at 12 months, and outer retinal morphology parameters obtained from SD-OCT and FAF, including RPD type, ONL thickness, ChT, CMT, and FAF changes. These will be analyzed using mixed-effects models to account for repeated measures at T0, 6 months, and 12 months, with fixed effects including treatment group, time, and treatment×time interaction. Robust standard errors clustered by participants will be used to account for correlation between eyes from the same participant. Adjustments will be made for baseline BCVA, age, sex, AMD stage, contralateral wet AMD status (yes/no), and other relevant factors. If assumptions of normality are not met, appropriate non-parametric methods or robust modeling approaches will be used.

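### Conversion to wet AMD is worded as signs present at 12 months and modelled as a reversible visit status, while the planning rates are incidences

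*Protocol article*

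**What the plan says.** Section 2.2.1 (Primary outcomes) defines the outcome as "conversion to wet AMD at 12 months (assessed by the presence of intraretinal fluid, subretinal fluid, pigment epithelial detachment" or subretinal hyperreflective material). The signs are listed without qualification. There is no reference to the T0 scan and no rule for an eye that showed a sign earlier and no longer does.

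Section 2.2 fixes the visits: "All patients will be evaluated at T0, 6- and 12-months follow-up", with SD-OCT at each.

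Section 2.3 places conversion in one list with the morphology measures and analyses them all by "mixed-effects models to account for repeated measures at T0, 6 months, and 12 months", with a treatment-by-time interaction. It adds: "The primary confirmatory timepoint will be 12 months".

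Table 1 admits "Patients with early or moderate dry AMD in one or both eyes". It does not mention pigment epithelial detachment (PED) at baseline.

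The sample size in section 2.3 rests on this: "Assuming a 12% progression rate in the solifenacin group and a 3% progression rate in the mirabegron group at 12 months". The same section says that "the expected 12-month conversion rate of 12% has been used as a planning value".

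The Introduction states that "Anti-VEGFs are effective in reducing exudation".

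**The concern.** Conversion from dry to wet AMD is naturally an event: it happens once and is then part of the eye's history. The written criterion describes a state at one visit, and the model allows that state to change in either direction between visits. This opens two routes to misclassification.

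- **Missed events.** An eye that shows fluid at or before month 6 and then receives anti-VEGF may have no fluid at month 12. The article itself says anti-VEGF reduces exudation. Nothing in the text carries the earlier conversion forward.
- **False events.** A listed sign counts by its presence, not its appearance. If a sign, most plausibly an unqualified PED, is already there at T0, an unchanged eye meets the month-12 criterion.

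The planned contrast leaves little room for either. At 133 per group the expected counts are about 16 and 4 converters (133 × 0.12 = 15.96; 133 × 0.03 = 3.99). Lost events cost power directly. False events, if equally common in both arms, add noise and dilute the relative effect.

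**Working it through.** **1. Endpoint against planning rates.** All the published rates quoted in section 2.3 count eyes that convert over a period:

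- 12-month conversion rates of 20.3% and 15.9% in high-risk fellow eyes
- cumulative incidences of about 26.2–32.2% over 96 weeks
- 3.2 and 15.2 per 100 person-years, without and with neovascularisation in the fellow eye

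Section 2.2.1 counts eyes with signs at month 12. The two quantities agree only if every converted eye still shows a listed sign at month 12 and no eye had one at T0. The article states neither condition.

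**2. The plan's own figure.** Inputs from section 2.3: p1 = 0.12, p2 = 0.03, two-sided α = 0.05, power 80%. In its standard form, with the whole numerator squared and p = (p1 + p2)/2 = 0.075:

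n = [1.960·√(2p(1−p)) + 0.8416·√(p1(1−p1) + p2(1−p2))]² / (p1 − p2)²

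= [1.960 × 0.3725 + 0.8416 × 0.3670]² / 0.09² = 133.3, rounded up to 134 per group.

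This reproduces the stated 134. The enrolment target of 156 less 15% leaves 156 × 0.85 = 132.6, about 133 per group.

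**3. Power with misclassification.** The formula is power = Φ{[√n·(p1 − p2) − 1.960·√(2p(1−p))] / √(p1(1−p1) + p2(1−p2))}, with n = 133. With no misclassification it gives Φ(0.839) = 79.9%.

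The article gives no misclassification rates. Those below are assumptions, taken as equal in both arms.

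*A share m of true converters shows no sign at month 12.* Observed rate = p(1 − m).

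| m | Observed rates | Power |
|---|---|---|
| 10% | 10.8% vs 2.7% | 75.2% |
| 20% | 9.6% vs 2.4% | 69.8% |
| 25% | 9.0% vs 2.25% | 66.8% |

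*A share f of eyes has a listed sign at T0 that is scored as conversion.* Observed rate = f + (1 − f)p.

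| f | Observed rates | Power |
|---|---|---|
| 2% | 13.76% vs 4.94% | 69.7% |
| 5% | 16.4% vs 7.85% | 57.0% |

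**4. After the change.** With an incident, cumulative definition the planning rates stay at 12% and 3%, so n stays at 134 and nothing in the sample size has to move.

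**The case against.** The strongest reply is that the article means incident conversion. Study eyes enter with dry AMD, so the word conversion already implies a change, and a conversion rate at 12 months is ordinary shorthand for a rate by 12 months. The planning paragraph uses the same phrase for its own rates. On that reading endpoint and planning agree. This is probably the intent. It does not tell two centres how to score a treated eye that is now dry, and the repeated-status model with month 12 as the confirmatory visit points the other way.

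A reader might infer that the plan has decided to ignore conversions before month 12. The documents do not support that. SD-OCT is scheduled at month 6, so a conversion visible then is recorded, and nothing directs that it be rescored. What is missing is the rule that keeps it.

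A reader might also infer that baseline PED will inflate the event count. That goes too far. PED is listed as a sign of wet AMD and study eyes must have dry AMD, so a strict grader could exclude such eyes at entry. That some PED occurs in dry AMD is clinical knowledge from outside the article. What stands is narrower: PED is unqualified, and no listed sign has to be new.

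The missed-event route has limits as well. The article does not describe how converted study eyes are treated, and two of the four signs are not fluid, so an eye may still meet the criterion after anti-VEGF. A scenario in which every early converter is missed is therefore not credible as a forecast.

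Finally, the full protocol may hold grading rules that this article leaves out. But the article does state a criterion and a model, and it is those that do not fit the planned quantity.

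**Conclusion.** The point holds as a defect of definition. As worded, the main outcome is presence of signs at one visit, analysed as a status that can reverse, while the sample size assumes incidence. Misclassification in both directions is possible under the literal text. It is not shown to occur, and its rate cannot be estimated from the article.

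The power figures show sensitivity only: from 80% to about 75% if 10% of converters are missed, about 67% if 25% are missed, and about 70% with 2% false positives per arm. They rest on assumed rates equal in both arms and on an unadjusted test of independent observations. The planned analysis is adjusted, clustered by participant and Holm-corrected, so these are not estimates of the trial's actual power. The sample-size arithmetic is not in question here.

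The change is worth making before outcome grading starts, because it settles the scoring of the main outcome at very little cost.

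**What to change.** In section 2.2.1, define conversion as the earlier of:

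- the first appearance, at any visit up to and including month 12, of intraretinal fluid, subretinal fluid, PED or subretinal hyperreflective material that was absent from that eye on the T0 SD-OCT (a PED counts only if new since T0)
- a recorded start of anti-VEGF in the study eye for wet AMD, up to month 12

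State that once either is met the eye stays converted, whatever later imaging shows.

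In section 2.3, take conversion out of the repeated-status model and analyse the cumulative 12-month outcome per eye, keeping the planned covariate adjustment and participant-level clustering.

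Cost: a wording change and one case-report field for the date of conversion or anti-VEGF start. The scheduled scans suffice for visits at T0, 6 and 12 months. Events between visits depend on clinic records, so their capture may be incomplete, and both centres should collect them in the same way in both groups. The sample size does not change.

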In this respect, our preliminary findings in the model of oxygen-induced retinopathy suggest a major effect of β3-AR in inhibiting proangiogenic signaling and favoring endothelial cell homeostasis by activating nitric oxide bioavailability through β3-AR coupling to the nitric oxide synthase pathway (15). Considering that β3-AR activation triggers a cascade of events that, in the bladder, leads to detrusor muscle relaxation while, in the retina, plays a pèotential role in regulating neovessel proliferation in response to an ischemic insult, we hypothesized that β3-AR stimulation with mirabegron could be useful to prevent dry AMD from transitioning to wet AMD by impeding the development of leaky new blood vessels in the macula (Figure 2).

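### The conversion endpoint counts pigment epithelial detachment and subretinal hyperreflective material without requiring that they be new or neovascular, so it is broader than the event the trial is about

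*Protocol article*

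**What the plan says.** - **Event.** Section 2.2.1 (Primary outcomes) has conversion to wet AMD at 12 months "assessed by the presence of intraretinal fluid, subretinal fluid, pigment epithelial detachment, subretinal hyperreflactiva material". The list has no conjunction. It gives no PED type, no qualifier on SHRM and no condition that a sign be absent at T0.
- **Imaging.** Section 2.2 states that "all patients will be evaluated using spectral domain optical coherence tomography (SD-OCT) and fundus autofluorescence (FAF"). The visits at T0, 6 and 12 months are conducted "with a complete ophthalmic examination, including SD-OCT, FAF, and microperimetry". Slit lamp and indirect ophthalmoscopy are also listed. The article names no angiographic test.
- **Population.** Table 1 admits "Patients with early or moderate dry AMD in one or both eyes". PED or SHRM at baseline is not among the exclusions.
- **Assessor.** Section 2.1 says "ophthalmologists will be blinded regarding which patients have been treated with both drugs".
- **Target of the hypothesis.** The Discussion proposes that mirabegron could "prevent dry AMD from transitioning to wet AMD by impeding the development of leaky new blood vessels in the macula".
- **Planning rates.** Section 2.3 draws on published rates of conversion. One source is explicitly neovascular: it "reported progression to choroidal neovascularization (CNV) of approximately 3.2 per 100 person-years in bilateral early/intermediate AMD". The sample size then rests on "Assuming a 12% progression rate in the solifenacin group and a 3% progression rate in the mirabegron group at 12 months (absolute difference 9" points).

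**The concern.** Intraretinal or subretinal fluid is reasonable structural evidence of exudation. PED and SHRM are less specific. In early or moderate dry AMD, drusen can merge into a drusenoid PED, and vitelliform material can appear as SHRM, with no new vessel present. A centre that applies the text of 2.2.1 as written may score such an eye as wet AMD, and a centre that uses its own judgement may not. The measured event is then wider than the neovascular event in the Discussion and in the choroidal neovascularization rates cited in 2.3.

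Three things are at stake: the meaning of the reported conversion rate, agreement between the two centres, and the power of the main comparison, which was planned on 12% against 3%. Because the planned mirabegron rate is so low, even a small number of non-neovascular events would make up a large part of what is counted in that group.

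**Working it through.** **Inputs.** Section 2.3 gives p1 = 0.12 (solifenacin), p2 = 0.03 (mirabegron), two-sided alpha 0.05, power 80% and 134 per group net. The share f of eyes without true conversion that gain a non-neovascular PED or SHRM is not in the documents. It is assumed here and shown as a range.

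**Step 1: reproduce the plan's figure.** In the standard two-proportion formula the whole numerator is squared (the exponent is misplaced in the printed version):

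n = [1.96 √(2p̄(1−p̄)) + 0.8416 √(p1(1−p1) + p2(1−p2))]² / (p1−p2)², with p̄ = 0.075

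= (0.7301 + 0.3089)² / 0.0081 = 133.3, so 134. This agrees with the plan.

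Power at 134 = Φ{[0.09 √134 − 0.7301] / √0.1347} = Φ(0.849) = 80.2%.

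**Step 2: add non-neovascular events equally to both groups.** Observed rate = p + (1−p)f. For f = 2%:

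- solifenacin: 0.12 + 0.88 × 0.02 = 0.1376
- mirabegron: 0.03 + 0.97 × 0.02 = 0.0494
- power: Φ{[0.0882 √134 − 0.8070] / 0.4070} = Φ(0.526), about 70%

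| Assumed f | Solifenacin | Mirabegron | Difference (points) | Risk ratio | Power at 134 | n per group for 80% |
|---|---|---|---|---|---|---|
| 0 | 12.0% | 3.0% | 9.0 | 0.25 | 80% | 134 |
| 1% | 12.9% | 4.0% | 8.9 | 0.31 | 75% | 152 |
| 2% | 13.8% | 4.9% | 8.8 | 0.36 | 70% | 170 |
| 5% | 16.4% | 7.9% | 8.6 | 0.48 | 57% | 228 |

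**Step 3: make-up of the counted events.** The non-neovascular share of mirabegron-group events is 0.97f / (0.03 + 0.97f). At f = 2% it is 0.0194 / 0.0494 = 39%. At f = 5% it is 0.0485 / 0.0785 = 62%.

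**Step 4: test the assumption of no drug effect on dry lesions.** Suppose instead that the drug reduces these lesions by the same risk ratio of 0.25. At f = 2% the mirabegron rate is then 0.03 + 0.97 × 0.005 = 0.0349, against 0.1376. Power is about 85%, a gain rather than a loss.

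**Step 5: test a fix that goes too far.** If a stricter rule missed 20% of true events in both groups, the rates would be 9.6% and 2.4%, with power about 70%. A 10% loss gives 10.8% and 2.7%, with power about 76%.

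These figures treat each participant as one independent unit. They ignore the Holm adjustment and the correlation between eyes.

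**The case against.** The strongest reply is that the endpoint is conversion to wet AMD and the four signs only say how it is assessed. The article never writes that any single sign suffices, and nothing obliges an ophthalmologist who judges a PED drusenoid to call it wet. Grading details are also commonly left to a fuller protocol. Part of this stands: a reader might infer that any PED or SHRM must be scored as conversion, but the text only permits that reading. What remains is that the signs are fixed in the article without the qualifier, and two centres can read them differently.

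A reader might also infer that SD-OCT and FAF cannot identify neovascular lesions. That goes too far. Structural OCT can suggest a neovascular PED, for example when fluid is present, and the visits include a fundus examination. PED or SHRM alone is simply not specific.

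The third tempting inference is that dilution is established. It is not. The Introduction speaks of slowing AMD progression in general, and the Discussion proposes an effect on choroidal hypoperfusion, upstream of new vessels. If dry lesions respond too, the loss can disappear (Step 4). In addition, f has no source, the planned effect is stated as an absolute difference, and that difference barely moves. Finally, most rates cited in 2.3 are given as conversion or cumulative incidence, and their event definitions cannot be seen here; only one cohort is explicitly described in terms of choroidal neovascularization.

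**Conclusion.** The concern holds as a fault in the endpoint definition. As worded, 2.2.1 lets non-neovascular lesions of dry AMD count as conversion, with no angiography to sort them out, so the event can be broader than the one in the hypothesis. The sample-size figure of 134 is arithmetically sound.

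The size of the effect is conditional. It rests on an assumed f, on equal misclassification in both groups (plausible given the blinded ophthalmologists) and on no drug effect on dry lesions. Under those conditions, f between 1% and 5% takes power from 80% to between about 75% and 57% and the risk ratio from 0.25 to between 0.31 and 0.48. The absolute difference loses less than half a point. The documents do not support a claim that the trial is underpowered by a known amount. They do support tightening the definition before grading begins.

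**What to change.** In 2.2.1, count PED or SHRM as conversion only when it is new since T0 and graded as neovascular by the blinded ophthalmologist, under one written rule used at both centres. State that an isolated drusenoid PED or vitelliform material does not count, and record isolated non-neovascular lesions in their own field as dry AMD progression. Report two sensitivity analyses: the four-sign definition as now written, and a definition that requires intraretinal or subretinal fluid.

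Do not let the primary event depend on angiography done only in some patients. Who receives it may differ by centre and, in a non-randomized study, by group. A fluid requirement is better kept as a sensitivity analysis, because losing true events also costs power (Step 5).

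The cost is a change of wording, a short grading rule and an extra form field, with no added procedure. The downside is some grading judgement, and a few early neovascular lesions may be misclassified.
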